## Abstract

**Background:**

Development of longer term stroke rehabilitation services is limited by lack of evidence of effectiveness for specific interventions and service models. We describe the protocol for a multicentre randomised controlled trial which is evaluating an extended stroke rehabilitation service. The extended service commences when routine ‘organised stroke care’ (stroke unit and early supported discharge (ESD)) ends.

**Methods/design:**

This study is a multicentre randomised controlled trial with health economic and process evaluations. It is set within NHS stroke services which provide ESD. Participants are adults who have experienced a new stroke (and carer if appropriate), discharged from hospital under the care of an ESD team.

The intervention group receives an extended stroke rehabilitation service provided for 18 months following completion of ESD. The extended rehabilitation service involves regular contact with a senior ESD team member who leads and coordinates further rehabilitation. Contact is usually by telephone. The control group receives usual stroke care post-ESD. Usual care may involve referral of patients to a range of rehabilitation services upon completion of ESD in accordance with local clinical practice. Randomisation is via a central independent web-based service.

The primary outcome is extended activities of daily living (Nottingham Extended Activities of Daily Living Scale) at 24 months post-randomisation. Secondary outcomes (at 12 and 24 months post-randomisation) are health status, quality of life, mood and experience of services for patients, and quality of life, experience of services and carer stress for carers. Resource use and adverse events are also collected. Outcomes are undertaken by a blinded assessor.

Implementation and delivery of the extended stroke rehabilitation service will also be described. Semi-structured interviews will be conducted with a subsample of participants and staff to gain insight into perceptions and experiences of rehabilitation services delivered or received.

Allowing for 25% attrition, 510 participants are needed to provide 90% power to detect a difference in mean Nottingham Extended Activities of Daily Living Scale score of 6 with a 5% significance level.

**Discussion:**

The provision of longer term support for stroke survivors is currently limited. The results from this trial will inform future stroke service planning and configuration.

**Trial registration:**

This trial was registered with ISRCTN (identifier: ISRCTN45203373) on 9 August 2012.

## Background

There are approximately 300,000 disabled stroke survivors in the UK [1]. Although one third of patients remain disabled 12 months after acute stroke, the longer term provision of stroke rehabilitation is sparse. Input from a therapist or nurse with specialist expertise in stroke rehabilitation is rare beyond 6 months post-discharge. Stroke patients and their informal carers are frequently disappointed and frustrated that longer term rehabilitation is not more widely available, and the UK Stroke Survivor Needs Survey reported that nearly half of stroke survivors experience unmet needs in the longer term [2].

Stroke units and early supported discharge (ESD) services are effective ways to improve patient outcomes and the quality of care following stroke [3,4]. These services are referred to as ‘organised stroke care’, and their key features are multidisciplinary stroke specialist expertise and coordination of care [5,6]. In contrast, there is no clear evidence of the clinical and cost effectiveness of longer term rehabilitation following stroke [7]. A Cochrane review of therapy-based rehabilitation services for patients living at home more than one year after stroke concluded that it was unclear whether rehabilitation provided after one year can improve recovery [8]. However, therapy-based rehabilitation services for stroke patients at home provided soon after discharge have been shown to be effective [9].

ESD services offer patients the opportunity to continue rehabilitation in their own home following a period of stroke unit care. ESD provided by a specialist multidisciplinary team leads to better clinical outcomes, increased satisfaction with care and reduced NHS costs [3]. ESD is a core component of an evidence-based stroke service, and it is the current ‘gold standard’ for an early community rehabilitation service for stroke patients with ongoing rehabilitation needs who are discharged to their own homes [10]. Typically, an ESD team becomes involved with discharge planning with patient, family and stroke unit staff at an early stage of admission. Prior to discharge from hospital, a member of the team may undertake a home visit (with the patient) or an environmental visit (without the patient). Rehabilitation and ongoing care provided by a specialist ESD team begins immediately after discharge. The duration and intensity of ESD therapy depends upon patient need. The discharge policy of ESD services varies, with some services defining a maximum period of input of three months. ESD teams do not usually retain any contact or involvement with patients once their input has ceased. Following discharge from ESD services, the concept of organised stroke care disappears. Patients who have ongoing rehabilitation needs may be referred to a range of services, most of which do not offer specialist stroke rehabilitation, such as neurorehabilitation teams, day hospitals and community rehabilitation services. This research study is evaluating an extended stroke rehabilitation service which commences when ESD ends. The service is delivered by existing ESD teams and extends organised stroke care beyond ESD.

## Methods/design

### Study aim and objectives

This study aims to determine the clinical and cost effectiveness of an extended stroke rehabilitation service. The objectives of the study are as follows:To determine whether an extended stroke rehabilitation service (intervention) improves patient outcomes compared to usual care (control). The primary outcome is extended activities of daily living (EADL) at 24 months following randomisation. Secondary outcomes are: health status, quality of life, mood and experience of services (12 and 24 months following randomisation).To determine whether an extended stroke rehabilitation service improves carer outcomes compared to usual care. Outcomes are: quality of life, carer stress and experience of services (12 and 24 months following randomisation).To determine the cost effectiveness of an extended stroke rehabilitation service.To document how the extended stroke rehabilitation service is implemented and delivered in different settings.To seek the views and experiences of patients, carers and rehabilitation staff about the community rehabilitation they have received or provided.To explore the impact of the severity of activity limitation, pre-stroke heath status and comorbidity upon the effectiveness of the intervention.

### Study design

This study is a pragmatic, observer-blind, parallel group, multicentre, randomised controlled trial with health economic and process evaluations. Figure 1 summaries the study methods.

**Figure 1 Fig1:**
[figure not shown]
Study summary. ESD: Early Supported Discharge. NEADL: Nottingham Extended Activities of Daily Living Scale. OHS: Oxford Handicap Scale. HAD: Hospital Anxiety and Depression Scale.

### Study setting

The study is being conducted in National Health Service (NHS) stroke services that provide ESD. To be eligible to take part, ESD services must meet the following criteria:The ESD service is a multidisciplinary stroke team who provide community rehabilitation following discharge from hospital.The ESD service provides stroke rehabilitation at home within 48 hours of patient discharge from hospital.The ESD service provides stroke rehabilitation for a specified period of time and/or has clear criteria for discharge of patients from the service.

### Study participants

Adults who have experienced a stroke and who fulfil the following criteria are eligible:

#### Inclusion criteria

Aged 18 years and over,Confirmed diagnosis of new stroke (first ever or recurrent),Will be discharged from hospital under the care of an ESD team or are currently receiving this service.

#### Exclusion criteria

Unable to participate in a rehabilitation programme which focuses upon EADL

A carer is the main family member or friend, who will provide support after discharge. He or she may not necessarily be co-resident with the patient. If a stroke patient has no carer or a carer does not wish to participate in the study, the patient may still participate in the study.

### Case ascertainment, recruitment and consent

#### Patients

Potential patients are identified and recruited by NHS staff (clinicians, staff from the Local Clinical Research Network (LCRN) and senior members of the ESD team) at each participating NHS centre. Potential patients may be recruited prior to discharge from hospital or whilst receiving care from an ESD service. Although the extended stroke rehabilitation service does not commence until routine ESD services end, identification and recruitment of patients in hospital or during ESD maximises recruitment opportunities.

#### Consent for patients with mental capacity

For potential participants with mental capacity to consent to research, NHS staff approach the patient, discuss the study and provide a study information sheet. After allowing sufficient time for potential participants to decide whether to take part in the study (over 24 hours) and an opportunity to ask questions, consent is obtained in writing. Where a patient has mental capacity but is unable to sign the consent form (for example, because of weakness of the dominant hand following stroke), consent is confirmed orally in the presence of a witness (an individual not otherwise involved in the trial), who signs the consent form on behalf of the participant.

#### Consent for patients with aphasia

In order to include stroke patients with communication difficulties due to aphasia in this study, a set of ‘easy access’ study documentation was specifically developed. To recruit and consent patients with aphasia, NHS staff approach the patient, discuss the study and provide them with the easy access information sheet. After allowing sufficient time for the information to be considered (over 24 hours) and an opportunity to ask questions, consent is obtained in writing using the easy access consent form.

#### Consent for patients without mental capacity

Stroke patients who do not have mental capacity can also take part in this study. As patients with mental incapacity often have more disabling strokes, we believe that they may benefit from the extended stroke rehabilitation service. To recruit patients lacking in mental capacity, NHS staff identify a personal consultee to approach and discuss the study with. This is a person who is in a position to advise on the wishes and feelings of the potential patient in relation to taking part in this research project. The identified consultee is provided with a consultee information sheet. After allowing sufficient time to consider the patient’s wishes and feelings (over 24 hours) and an opportunity to ask questions, the consultee is asked to complete a consultee declaration form if they believe the patient would have no objection to taking part in the study.

If a patient regains capacity during their participation in the study, they will be informed about the study, given a ‘recovered capacity’ patient information sheet and asked to provide their own consent to continue in the study on a recovered capacity consent form. If a patient does not wish to continue in the study, they will be withdrawn. Data collected prior to withdrawal will be used in the study analysis.

Due to the nature of this study, potential patients lacking in capacity also need to have a relative or friend (carer) who is prepared to assist with the extended stroke rehabilitation service reviews and outcome assessments, as these are unlikely to be possible without their support.

#### Loss of capacity to consent to research during participation in the study

If a patient who has provided their own consent loses capacity to consent to research during their participation in the study, advice will be sought from a personal consultee about their continuing participation in the study. This will be a person who is in a position to advise on the wishes and feelings of the patient in relation to the research study. On entering the study, patients are asked to nominate a relative or friend who they would like to be their consultee should they lose capacity to consent to research. In the event of loss of capacity to consent to this research, the nominated consultee will be given a ‘loss of capacity’ consultee information sheet. If a consultee believes the patient would have no objection to continuing in the study, they will be asked to complete a loss of capacity consultee declaration form. If the consultee believes that the patient would not wish to continue in the study, the patient will be withdrawn from the study. Data collected prior to withdrawal will be used in the study analysis.

#### Carers

Potential carers are identified by ESD senior team members whilst the patient is receiving routine ESD care. At the time of patient discharge from routine ESD services, if the patient has an identified carer, he or she is provided with an invitation letter, study information sheet, study carer baseline questionnaire and pre-paid envelope (addressed to the study coordinating centre). Provision of the invitation letter and study documents may be in person by an ESD senior team member, by post by the local study team or by a consented patient. These three options are used to maximise potential opportunities for carers to take part in the study as carers are not always present at staff visits. The invitation letter asks a carer to complete and return the baseline questionnaire, if he or she is willing to participate in the study.

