### Baseline assessment

A patient baseline assessment is performed by NHS staff at discharge from routine ESD services and immediately prior to randomisation. The following data is collected: date of hospital discharge, date of ESD discharge, Abbreviated Mental Test Score [17], Sheffield Aphasia Screening Test [18], EADL (Nottingham EADL Scale [11]), health status (Oxford Handicap Scale [12]), quality of life (EuroQol EQ-5D [19]) and mood (Hospital Anxiety and Depression Scale [20]).

Carers receive a baseline questionnaire with the study invitation letter. The questionnaire collects the following data: demographic data, quality of life (EuroQol EQ-5D [19]) and carer stress (Caregiver Strain Index [21]).

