### Randomisation

Randomisation is by a central independent web-based service hosted by Newcastle University Clinical Trials Unit. Participants are stratified according to stroke service and randomised to either the intervention or control group in a 1:1 ratio using permuted block sequences. Stroke patients and carers are randomised as a single unit.

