### Blinding

Due to the nature of the intervention, it is not possible to blind stroke patients or carers to treatment allocation. Where patient outcome assessments are undertaken by telephone or face to face, it is intended that they are conducted blinded to treatment allocation. After each assessment the assessor is asked to record whether they have unintentionally become aware of treatment allocation due to conversation with the participant. Success of patient outcome assessment blinding will be reported.

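### The protocol does not secure carers' agreement and baseline before randomisation, so the carer comparison is open to selection after allocation

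*Protocol article*

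**What the plan says.** All of these statements are in the protocol article.

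- **Identification (Carers).** "Potential carers are identified by ESD senior team members whilst the patient is receiving routine ESD care". This is before the patient is randomised.
- **Invitation (Carers).** "At the time of patient discharge from routine ESD services, if the patient has an identified carer, he or she is provided with" a pack: invitation, information sheet, baseline questionnaire and a reply envelope addressed to the coordinating centre.
- **Delivery (Carers).** Provision "may be in person by an ESD senior team member, by post by the local study team or by a consented patient". The reason given for three routes is that carers may be absent when staff call.
- **Joining (Carers).** "The invitation letter asks a carer to complete and return the baseline questionnaire, if he or she is willing to participate in the study". No deadline relative to randomisation is set.
- **Patient baseline (Baseline assessment).** "A patient baseline assessment is performed by NHS staff at discharge from routine ESD services and immediately prior to randomisation". The carer questionnaire covers demographics, EQ-5D and the Caregiver Strain Index, and its timing relative to randomisation is not stated.
- **Randomisation.** "Stroke patients and carers are randomised as a single unit".
- **Blinding.** "it is not possible to blind stroke patients or carers to treatment allocation".
- **Analysis (Secondary analyses).** Secondary outcomes are compared by linear regression with site terms and patient-level covariates, of which baseline scores are the example. No carer score is named.

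Study aim and objectives makes carer quality of life, stress and experience of services at 12 and 24 months a between-group comparison.

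**The concern.** Randomisation makes two groups comparable only if membership of those groups is settled without knowledge of the allocation. Here the carer group is settled by who posts a questionnaire back, and the pack first reaches the carer at the event where the patient is allocated.

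Two things could go wrong.

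1. **Selection.** A carer who learns that the patient will have 18 months of further contact may be more willing, or less, to take part than one who learns that the patient will not. That willingness may depend on how strained the carer is. The pack may also be handed over by a senior ESD team member, the same role that delivers the intervention, so invitation itself could differ by arm. The carers analysed could then differ between arms before any treatment effect.
2. **Contaminated baseline.** Strain and quality of life rated after hearing the allocation may already reflect it. Adjusting for such a score can hide an effect or create one.

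What is at stake is the interpretation of objective 2.

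**Working it through.** **Step 1: order of events.**

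| Event | Time stated | Section |
|---|---|---|
| Carer identified | during routine ESD | Carers |
| Carer pack first provided | at ESD discharge | Carers |
| Patient baseline | at ESD discharge, immediately before randomisation | Baseline assessment |
| Patient randomised | straight after that baseline | Baseline assessment |
| Carer decides, completes and returns questionnaire | no time stated; return is by post | Carers |

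Pack provision and randomisation share one event. For a pack that is posted, or passed on by the patient, completion before an immediate randomisation is unlikely. For a pack handed over in person it is possible but not required. No section holds back randomisation, or disclosure of the allocation, until the carer has replied.

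**Step 2: what the document allows to be calculated.** It gives no carer sample size, response rate or standard deviation, so it has no figure of its own on this point to reproduce. Its only sample size concerns patients, and that is sound. With a difference of 6, SD 18, two-sided 5% and 90% power, n per arm = 2 × (1.960 + 1.282)² × (18/6)² ≈ 189.2, rounded up to 190, or 380 in total against the stated 382. Allowing for 25% attrition, 382/0.75 = 509.3, so 510.

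**Step 3: illustration on assumed values.** Let prior strain be standard normal, with correlation r to the propensity to reply, and let a proportion q reply. Mean strain among those replying is r × φ(z_q)/q, where z_q is the normal quantile of q.

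- q = 0.65 (assumed, intervention): 0.370/0.65 = 0.570
- q = 0.50 (assumed, control): 0.399/0.50 = 0.798

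| r, intervention | r, control | Spurious difference (size, SD) |
|---|---|---|
| 0.2 | 0.2 | 0.2 × (0.798 − 0.570) = 0.046 |
| 0.3 | 0.3 | 0.3 × (0.798 − 0.570) = 0.068 |
| 0 | 0.3 | 0.3 × 0.798 = 0.239 |
| −0.1 | 0.3 | 0.239 + 0.1 × 0.570 = 0.296 |

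**Step 4: a second selection model.** Replying follows a logistic model with a slope per SD of prior strain, simulated with 2,000,000 draws. Again every input is assumed.

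| Reply rate, intervention v control | Slopes, intervention v control | Difference (size, SD) |
|---|---|---|
| 70% v 70% | 0.5 v 0.5 | 0.001 |
| 70% v 60% | 0.5 v 0.5 | 0.046 |
| 70% v 50% | 0.5 v 0.5 | 0.092 |
| 70% v 50% | 0 v 0.5 | 0.236 |
| 70% v 50% | 0.25 v 0.75 | 0.259 |

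The two models agree. Unequal response alone, with the same dependence on strain in both arms, gives less than 0.1 SD. A difference of 0.2–0.3 SD needs the dependence on strain itself to differ by arm. These are unadjusted differences in prior strain. How much reaches the 12- and 24-month outcomes depends on how strongly prior strain predicts them and on what is adjusted for. The harm from a contaminated baseline covariate is not quantified here.

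**The case against.** The strongest objections, and what stands of each:

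- **The order is inferred.** A reader might infer that carers are invited by post, after randomisation, and complete the baseline knowing the arm. The document does not say so. In-person provision is allowed, a pack handed over at the discharge visit could be completed first, and the Blinding section says only that blinding is impossible, not when allocation becomes known. This is also a condensed article, and a fuller protocol may fix the sequence. This stands, and it limits the point to what the article fails to secure. It does not remove the point, because the timing that the article does state puts the pack and the randomisation at one event.
- **The model names no carer baseline.** A reader might infer that the analysis adjusts for a post-randomisation carer score. Secondary analyses mentions patient-level covariates only. This stands: the risk arises only if carer baseline scores are used, although they are the natural choice for carer outcomes.
- **The single-unit statement may be correct.** A reader might take it to be false. Its natural reading is that the carer takes the patient's allocation and is not randomised separately, which holds whenever the carer replies. This stands. The sentence needs clarifying, not deleting.
- **The sizes are assumed.** This stands. It is also tempting to set 0.3 SD beside the trial's design effect of 6/18 = 0.33 SD, but that effect belongs to the patient Nottingham EADL score and is no yardstick for carers.
- **Change may be late or disruptive.** By February 2015, 541 patients had been recruited, and making randomisation wait for a carer's reply could delay it or lose carers. This stands in part. Recruitment was to run until summer 2015, and recruitment can precede randomisation by several weeks, so some carers could still be reached earlier. Randomisation should not wait for them.

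**Conclusion.** The concern holds in a limited form: the protocol does not secure carer agreement and carer baseline before randomisation. Joining by later postal return while unblinded leaves the objective 2 comparison open to selection after allocation. If carer baseline scores are used as covariates, some may be post-randomisation measures.

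The document cannot show how many carers are affected or how large the bias is. Under the assumed response rates it is near 0 to 0.09 SD if replying depends on strain alike in both arms, and about 0.2–0.3 SD if that dependence differs by arm. The protocol's timing does not prevent the second case, and nothing in the document shows that it occurs.

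Only carer outcomes are touched. The patient primary analysis and the sample size of 510 are unaffected. The change is worth making because it is cheap and because, without it, a reader cannot tell whether randomisation protects the carer comparison.

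**What to change.** 1. **Carers still to be approached.** Provide the existing pack during ESD, when carers are already identified, and seek its return before the patient is randomised. Do not delay randomisation for a carer who has not replied.
2. **All carers.** Compare the questionnaire completion date with the randomisation date. Report carers identified, invited and replying, by arm.
3. **Main carer model.** Adjust for site and the patient's pre-randomisation scores, using one covariate set for every carer. Covariates should not be chosen carer by carer according to return date.
4. **Sensitivity analysis.** Restrict to carers whose questionnaire predates randomisation and adjust for carer baseline there. This subset is defined by something fixed before allocation, so it checks both the selection and the baseline problem.
5. **Randomisation section.** State that carers take the patient's allocation and may enter after it.

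Cost: a slightly earlier carer baseline for some, a few reminders, a date check and one extra analysis. The main carer model may lose precision where carer baseline is left out, and it cannot remove selection on unmeasured strain among late entrants, which is why the flow by arm and the restricted analysis are needed beside it. Carers already enrolled can be helped only by items 2 to 4.
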